	To assess whether monthly multidisciplinary telemedicine visits in addition to a multidisciplinary, personalized treatment plan including mobile palliative care - Attenuate the baseline to 6-, 12- and 18-months QoL worsening - Attenuate the progression of motor and non-motor MSA symptoms, including time to clinical milestones in prospectively recruited MSA individuals compared to sex-, age- (± 5 years), and disease duration-(± 12 months) matched MSA individuals from the historical EMSA-SG cohort^a^ and to prospectively recruited MSA individuals receiving in-person visits and mobile palliative care (as needed) only	- Baseline to 6- and 12-months EQ-5D-5L score change - Baseline to 6-, 12- and 18-months changes in the MSA-QoL total score and subscores - Baseline to 6-, 12- and 18-months change in motor and non-motor scales (total and subscores, including video-based, rater-blinded assessment of the UMSARS motor subscore and Hoehn & Yahr stage) - Time to clinical milestones (i.e., falls at least once a day, feeding by nasogastric tube or gastrostomy, unintelligible speech, indwelling catheter, wheelchair dependency)
	To assess whether monthly multidisciplinary telemedicine visits in addition to a multidisciplinary, personalized treatment plan including mobile palliative care - Reduce the number of medical complications - Reduce the caregiver burden - Provide an advantage in terms of benefit-harm and cost-effectiveness tradeoffs - Increase the individual satisfaction with the personalized treatment plan over the 18-months study period in prospectively recruited MSA individuals compared to prospectively recruited MSA individuals receiving in-person visits and mobile palliative care (as needed) only	- Number of medical complications (i.e., falls with or w/o injuries, urinary tract infections, choking, aspiration pneumonia, hospitalizations, death and others) over the 18-months study period - Baseline to 6-, 12- and 18-months change in the EQ-5D-5L score of informal caregivers of prospectively recruited MSA individuals - Baseline to 6-, 12- and 18-months change in PQoL Carers score and other caregiver-burden indicators in informal caregivers of prospectively recruited MSA individuals - Baseline and 12-months semi-structured online interview - Single-intervention and cumulative healthcare costs over the 18-months study period - Month 1 to 7, 13 and 18 SAPS change

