An overview of the study design is provided in Fig. 1, and the detailed MeDeMSA Care Visit Plan is reported in Table 2. After providing written consent, participants complete a home bladder and blood pressure (BP) diary for up to 72 h prior to the baseline visit, as well as a falls protocol referring to the month before the visit. During the baseline visit, participants undergo an in-person multidisciplinary assessment with the MeDeMSA Care study team. Following recommendations for PD settings (Bloem et al. 2021), the MeDeMSA Care team is composed of medical, neurorehabilitation, psychology, and palliative healthcare professionals with expertise in MSA care and is designed to meet the care needs that individuals with MSA may develop over the disease course. Baseline assessments include clinical, psychological, and neuro-rehabilitation evaluations, along with an online semi-structured interview on the individual healthcare preferences by the MeDeMSA team in Graz via a telemedicine platform currently used in the Tirol Kliniken [Computer-based Health Evaluation System, CHES, (Holzner et al. 2012)]. Additional tests, such as cardiovascular autonomic, sleep, urodynamic, or swallowing studies, are scheduled as needed during or shortly after the baseline visit. If not performed in the six months prior to the baseline visit, blood tests are conducted to check for undetected comorbidities (i.e., liver or renal failure) that could affect MSA medication dosages or require specific treatment (i.e., anemia, iron or vitamin deficiency). Following the baseline assessments, an individualized treatment plan is prepared using the MeDeMSA Care Operational Protocol (see Supplementary Material 1), which includes pharmacological and non-pharmacological measures, mobile palliative care for wheelchair-bound individuals, and guidance for self-practiced physiotherapy, occupational therapy, and speech therapy exercises (see Supplementary Materials 2, 3 and 4). The MeDeMSA Care Operational Protocol was developed by the MeDeMSA Care multidisciplinary study team based on available guidelines, consensus recommendations, scientific evidence and principles of good clinical practice. The protocol follows a “screen > diagnose > treat  with first-, second-, and third-line options” structure, designed to minimize the burden on recruited individuals and optimize healthcare resource allocation. Additionally, the treatment strategies are tailored to accommodate individual preferences, including the choice between pharmacological and non-pharmacological treatments, as well as among different types of pharmacological options or between tight symptoms’ control versus simplified medication schedules.

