**Table 2 Tab2:**
[figure not shown]
MeDeMSA Care Patient Visit Plan

During follow-up in-person visits at 6-, 12-, and 18-months, the therapeutic needs are reassessed and the treatment plan is adapted as required. If subjects cannot travel to the center, they are offered the possibility to complete the scheduled on-site assessments via the CHES online platform. At month-12, the semi-structured interview is repeated to evaluate changes in healthcare preferences due to disease progression. Follow-up calls are scheduled one month after each in-person visit (at months 1, 7, and 13) to verify treatment compliance and address barriers. Short Assessment of Patient Satisfaction (SAPS) surveys are administered online at months 1, 7, 13, and 18 to evaluate the overall individual satisfaction with the treatment plan. In case additional in-person visits are scheduled, the reason for such visits and eventual therapeutic adaptations are documented.

Upon completion of the baseline assessment, 23 patients are block-wise randomized to additionally receive monthly and on-demand telemedicine visits for neurological, psychological, and neurorehabilitation support via CHES. If the individuals randomized to receive additional telemedicine visits own a tablet or computer with a ≥ 10-inch display, they may use it to enhance digital comfort. Otherwise, a CE-certified tablet (e.g., SAMSUNG Tab A7 T505 LTE 32 GB) is provided. The MeDeMSA Care team members are asked to rate telemedicine feasibility and potential barriers beforehand. After each telemedicine visit, healthcare providers give feedback on how the visit was conducted, document any challenges encountered, and note the adopted strategies to solve them. Brief patient satisfaction surveys follow telemedicine and mobile palliative care interventions: these include a 0–10 rating scale for the overall satisfaction with the intervention and open-ended questions about its advantages and disadvantages. The MeDeMSA Care team holds regular meetings every six to eight weeks to review changes in the care needs of recruited individuals with MSA and coordinate additional support as required.

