### Randomization

To evaluate the feasibility of healthcare provision via telemedicine in MSA settings, recruited individuals with MSA are 1:1 block-randomized to receive either personalized best medical care with integrated mobile palliative interventions as needed (n = 23) OR personalized best medical care (including on demand mobile palliative interventions) PLUS telemedicine (n = 23). The randomization has a 2-strand stratification that accounts for the early (i.e., able to walk) versus advanced (i.e., wheel-chair bound) stage of MSA at the time of recruitment. The randomization sequence is kept concealed to the recruiting doctor until the baseline assessment is completed.

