### Analysis sets and subgroups

For the primary objective (see Table 1), we will compare the prospectively recruited MeDeMSA Care cohort with data from the historical EMSA-SG cohort (Wenning et al. 2013), matched by age (± 5 years), sex, and disease duration (± 12 months). Disease duration is defined as the time from the onset of motor symptoms or selected autonomic features, including orthostatic hypotension, urinary urge incontinence, or incomplete bladder emptying. If exact matching is not possible due to unavailable controls, an alternative matching approach by categorizing individuals into subgroups based on age (< 60 versus ≥ 60 years) and disease duration (< 3 vs. ≥ 3 years) will be applied. To better characterize the MeDeMSA Care cohort and, secondarily, enable detailed comparisons between personalized best medical care with and without telemedicine, the EQ-5D-5L tool has been chosen for the present study (Janssen et al. 2013; Feng et al. 2021). This offers five response levels: no/slight/moderate/severe/extreme problems. For comparisons with the historical cohort, which used the EQ-5D-3L with three response levels (no/moderate/extreme problems), EQ-5D-5L responses will be grouped post-hoc and consistently applied across assessments (van Hout et al. 2012).

For secondary objectives (see Table 2), the MeDeMSA Care cohort will be divided into early versus advanced MSA (i.e., wheelchair-bound at the time of recruitment), and further sub-grouped by sex (male versus female), MSA phenotype [parkinsonian versus cerebellar (Wenning et al. 2022)], age (< 60 versus ≥ 60 years), and disease duration (< 3 vs. ≥ 3 years) for exploratory purposes.

To explore the impact of telemedicine on various outcomes (QoL, symptom progression, complications, caregiver burden, costs, and individual satisfaction with the personalized treatment plan), exploratory comparisons will be made between the subgroup of individuals randomized to receive personalized best medical care and individuals receiving personalized best medical care PLUS monthly and on-demand telemedicine consultations, as well as between each of these subgroups and the historical EMSA-SG cohort.

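### For the randomised telemedicine comparison, satisfaction (SAPS) is defined only as change from month 1, a post-randomisation value, so any arm difference already present at month 1 is subtracted out

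*Protocol article*

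**What the plan says.** **Objective and measure.** In the Telemedicine rows of Table 1, one aim of adding monthly telemedicine is to "Increase the individual satisfaction with the personalized treatment plan over the 18-months study period", judged against the recruited patients who have in-person visits and palliative care only. The SAPS entry beside it is "Month 1 to 7, 13 and 18 SAPS change". The quality-of-life and caregiver change scores in the same cell start from baseline.

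**Timing.** Methods, Study design: "Upon completion of the baseline assessment, 23 patients are block-wise randomized to additionally receive monthly and on-demand telemedicine visits". The same section says that SAPS "surveys are administered online at months 1, 7, 13, and 18 to evaluate the overall individual satisfaction with the treatment plan". No SAPS at baseline is mentioned. The plan being rated does not exist before then: "Following the baseline assessments, an individualized treatment plan is prepared using the MeDeMSA Care Operational Protocol".

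**Status.** Under Analysis sets and subgroups, where satisfaction is among the outcomes named, "exploratory comparisons will be made between the subgroup of individuals randomized to receive personalized best medical care and individuals receiving" the same care plus telemedicine. The Randomization section gives 23 patients per arm.

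**The concern.** A change score is harmless in a randomised comparison when its starting value precedes randomisation, because the arms then differ at the start only by chance. SAPS follows the same change-score format as its neighbours in Table 1, but its starting value is collected about a month after allocation. Any effect of allocation on satisfaction by then becomes part of the reference and is removed from the result.

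An early effect is plausible here. The study is open label, satisfaction is self-reported, and one arm has been assigned monthly and on-demand telemedicine. Followed literally, the outcome could therefore return a null result for a real and lasting gain in satisfaction, or a negative one for a gain that shrinks but persists. The HTA row of Table 1 also lists changes in satisfaction indices, so a misleading contrast could be carried forward.

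**Working it through.** The article gives no SAPS effect size, standard deviation or power, so there is no stated figure to reproduce. The check is what the listed measure estimates, followed by an illustration on assumed inputs.

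**1. Order of events (from Study design).** Baseline assessment; randomisation on its completion; SAPS at months 1, 7, 13 and 18. All four SAPS values are post-randomisation.

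**2. What the measure estimates.** Let d1 be the between-arm difference (telemedicine minus no telemedicine) in mean SAPS at month 1, and dt the difference at month t = 7, 13 or 18.

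- Contrast of levels at month t: expectation dt.
- Contrast of changes from month 1: expectation dt - d1.

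The two agree only if d1 = 0. Writing f = d1/dt, the change contrast recovers (1 - f) of dt: 75% for f = 0.25, 50% for f = 0.50, 25% for f = 0.75 and 0 for f = 1.

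**3. Illustration.**

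- From the article: 23 per arm; significance level 0.05; 10% dropout, giving 23 × 0.9 = 20.7 per arm.
- Assumed: two-sided test, normal approximation, SAPS standard deviation set to 1, between-visit correlation rho of 0.3, 0.5 or 0.7, and the values of d1 and dt.
- Standard deviation of a change: sqrt(2(1 - rho)), that is 1.18, 1.00 and 0.77.
- Standard error of a contrast: SD × sqrt(2/23) = SD × 0.295.
- Example for levels at dt = 0.8: 0.8/0.295 = 2.71; 2.71 - 1.96 = 0.75; power 0.77.

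Results with 23 per arm:

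| d1 | dt | Expected change contrast | Rejection rate, change (rho 0.3 / 0.5 / 0.7) | Rejection rate, level at t |
|---|---|---|---|---|
| 0 | 0.8 | 0.8 | 0.63 / 0.77 / 0.94 | 0.77 |
| 0.4 | 0.8 | 0.4 | 0.21 / 0.27 / 0.42 | 0.77 |
| 0.8 | 0.8 | 0 | 0.05 / 0.05 / 0.05 | 0.77 |
| 0.8 | 0.4 | -0.4 | 0.21 / 0.27 / 0.42, nearly all in the wrong direction | 0.27 |

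With 20.7 per arm, power for levels at dt = 0.8 is 0.73. The change contrast gives 0.59 to 0.91 in the first row, 0.19 to 0.38 in the second, and 0.05 in the third.

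**4. Reading the table.** In the first row the change contrast loses nothing and, at rho = 0.7, is more powerful than the level contrast. In the third row a constant benefit of 0.8 SD is rejected only at the type I error rate, whatever the correlation. In the last row satisfaction is higher with telemedicine at both visits, yet the expected contrast is negative.

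**The case against.** **Exposure before month 1 is inferred.** The text shown does not date the first telemedicine visit, and the visit plan in Table 2 is not available here. Monthly visits counted from baseline could begin at about month 1, together with the SAPS survey and the month-1 follow-up call. Month 1 could then be nearly unexposed, apart from on-demand use and knowledge of allocation. This stands. It limits what can be said about the size of d1, but not the algebra: if d1 = 0, the level contrast targets the same effect.

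**Month 1 is the earliest possible rating.** The rated plan is prepared only after the baseline assessments, so no pre-randomisation SAPS was available and month 1 is an understandable reference. This also stands, and is why a baseline SAPS is not the remedy. Randomised arms can be compared on levels without one.

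**The wording may be shorthand, or trajectory may be meant.** The Psychological aspects rows of Table 1 speak of comparing satisfaction at each of the four time points and then list the same change measure, so levels may have been intended. An increase over the study period could also be read as a trajectory. These readings are possible, but change is the only measure named for the between-arm objective. The repeated-measures and mixed models under Data analysis are specified for comparisons with the historical cohort and for caregivers, not for SAPS between arms.

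**Low stakes.** The comparison is exploratory, and all four SAPS scores are collected anyway. Both points are right and limit the weight of the concern.

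**Stronger readings.** A reader might infer that the outcome will show no effect or harm. That requires d1 equal to, or larger than, dt, and the article gives no SAPS time course. Potential study limitations does let patients outside the telemedicine arm replace in-person follow-ups with telemedicine when they can no longer travel, which could narrow later differences, but by an unknown amount. A reader might also expect telemedicine patients to be near the top of the scale by month 1; nothing in the article supports such a ceiling.

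**Conclusion.** The point holds as a defect in one stated outcome definition. For the randomised telemedicine comparison, change from month 1 estimates dt - d1 and not the between-arm difference in satisfaction dt. The loss runs from nil (d1 = 0) to total (difference constant from month 1), with a reversed sign if d1 exceeds dt. Where the trial lies in that range cannot be determined from the article. The power figures above rest on an assumed standard deviation, correlation and effect, and only illustrate the mechanism.

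This should be corrected because the measure can mislead when followed as written and the correction is nearly free. It is not a threat to the trial's main result: it concerns one exploratory comparison and leaves the primary EQ-5D outcome untouched.

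**What to change.** In the Telemedicine rows of Table 1, and in the analysis plan, define the between-arm satisfaction outcome as the SAPS level at months 1, 7, 13 and 18, compared by randomised arm. One suitable analysis is a repeated-measures model with month 1 included as an outcome, terms for arm, visit and arm by visit, and adjustment for the early/advanced stratum used in the randomisation. Name either the month-18 level or the average level over the visits as the contrast. Keep change from month 1 only as a within-arm description.

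The cost is one line in Table 1 and a matching line in the analysis plan. The same surveys at the same visits supply the data. The one trade-off is precision: if there were truly no difference at month 1 and visits were highly correlated, a single-visit level contrast would be less powerful than the change contrast (0.77 against 0.94 in the illustration at rho = 0.7).

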## Methods

### Study design

This 18-month, monocentric, open-label study evaluates the impact of multidisciplinary, personalized best medical care, including mobile palliative and telemedicine support on the EQ-5D-5L score change of prospectively recruited MSA individuals compared to a sex-, age- and disease-duration matched historical European MSA cohort that received standard care [EMSA-SG cohort, (Wenning et al. 2013)], and whose data is stored at the Medical University of Innsbruck. The EMSA-SG cohort included individuals with MSA from ten countries, who underwent in-person assessments every six months over a 24-month period, showed largely comparable clinical-demographic characteristics across countries, but did not regularly receive treatment for MSA non-motor symptoms, neurorehabilitation, psychological counselling or palliative care offer (Kollensperger et al. 2010).

The study also assesses the participants'motor progression over 18 months using the Unified MSA Rating Scale (UMSARS) Part II through blinded video evaluations. Their progression is then compared to the motor progression curves of matched individuals from the EMSA-SG cohort.

An overview of the study design is provided in Fig. 1, and the detailed MeDeMSA Care Visit Plan is reported in Table 2. After providing written consent, participants complete a home bladder and blood pressure (BP) diary for up to 72 h prior to the baseline visit, as well as a falls protocol referring to the month before the visit. During the baseline visit, participants undergo an in-person multidisciplinary assessment with the MeDeMSA Care study team. Following recommendations for PD settings (Bloem et al. 2021), the MeDeMSA Care team is composed of medical, neurorehabilitation, psychology, and palliative healthcare professionals with expertise in MSA care and is designed to meet the care needs that individuals with MSA may develop over the disease course. Baseline assessments include clinical, psychological, and neuro-rehabilitation evaluations, along with an online semi-structured interview on the individual healthcare preferences by the MeDeMSA team in Graz via a telemedicine platform currently used in the Tirol Kliniken [Computer-based Health Evaluation System, CHES, (Holzner et al. 2012)]. Additional tests, such as cardiovascular autonomic, sleep, urodynamic, or swallowing studies, are scheduled as needed during or shortly after the baseline visit. If not performed in the six months prior to the baseline visit, blood tests are conducted to check for undetected comorbidities (i.e., liver or renal failure) that could affect MSA medication dosages or require specific treatment (i.e., anemia, iron or vitamin deficiency). Following the baseline assessments, an individualized treatment plan is prepared using the MeDeMSA Care Operational Protocol (see Supplementary Material 1), which includes pharmacological and non-pharmacological measures, mobile palliative care for wheelchair-bound individuals, and guidance for self-practiced physiotherapy, occupational therapy, and speech therapy exercises (see Supplementary Materials 2, 3 and 4). The MeDeMSA Care Operational Protocol was developed by the MeDeMSA Care multidisciplinary study team based on available guidelines, consensus recommendations, scientific evidence and principles of good clinical practice. The protocol follows a “screen > diagnose > treat  with first-, second-, and third-line options” structure, designed to minimize the burden on recruited individuals and optimize healthcare resource allocation. Additionally, the treatment strategies are tailored to accommodate individual preferences, including the choice between pharmacological and non-pharmacological treatments, as well as among different types of pharmacological options or between tight symptoms’ control versus simplified medication schedules.

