Building on the multidisciplinary expertise in MSA care at the Medical University of Innsbruck and its national and international partners, the Medical Decision Making in Multiple System Atrophy (MeDeMSA) Care study has been launched. It aims to evaluate whether a personalized, multidisciplinary care model, integrating mobile palliative care and telemedicine support, can attenuate QoL decline in prospectively recruited individuals with MSA by alleviating the symptomatic burden, ensuring continuity of care, and prioritizing individual healthcare preferences. QoL changes over 18 months are captured with the European QoL Questionnaire – 5 Dimensions – 5 Levels [EQ-5D-5L, (Rabin and de Charro 2001; Feng et al. 2021)] and compared to a matched historical European MSA cohort that received standard care [European MSA Study GroupEMSA-SG, cohort (Wenning et al. 2013)].

Secondary objectives of the MeDeMSA Care study are to assess the acceptance, safety, and cost effectiveness of such an integrated healthcare model, and are detailed in Table 1, along with their respective outcome measures. We here aim at sharing the MeDeMSA Care study design and operational protocols.

**Table 1 Tab1:** Primary and secondary objectives of the MeDeMSA Care Study (left) and respective outcome measures (right)

	Objective	Outcome measure
Quality of life	*Primary*	
	Impact of a multidisciplinary, personalized treatment plan including mobile palliative care (as needed) on the baseline to 18-months change in QoL of prospectively recruited MSA individuals, compared to sex-, age- (± 5 years), and disease duration- (± 12 months) matched MSA individuals from the historical EMSA-SG cohort^a^	- Baseline to 18-months EQ-5D-5L score change
	*Secondary*	
	Impact of a multidisciplinary, personalized treatment plan including mobile palliative care (as needed) on the baseline to 6- and 12-months change in QoL of prospectively recruited MSA individuals, compared to sex-, age- (± 5 years), and disease duration-(± 12 months) matched MSA individuals from the historical EMSA-SG cohort^a^	- Baseline to 6- and 12-months EQ-5D-5L score change - Baseline to 6-, 12- and 18-months changes in the MSA-QoL total score and subscores

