### Population

We plan to recruit 46 individuals, who fulfill all the inclusion criteria listed below:i.Age ≥ 30 years at the time of consent;ii.Diagnosed with clinically probable OR clinically established MSA according to the current criteria of the International Parkinson Disease and Movement Disorder Society (Wenning et al. 2022);iii.Life-expectancy of at least 24 months as assessed by the investigator at the time of consent;iv.Understands and agrees to comply with the study procedures and provides written informed consent (Note: a legal representative may NOT provide consent on behalf of the subject);v.Signed and dated informed consent document;vi.Fluency in German;vii.If unable to walk or stand without assistance/support at the time of consent, the participant must live in Tyrol or in another Austrian region with available mobile palliative care.

Candidates are excluded from the study if they meet any of the following conditions:i.Participation in an interventional clinical study at screening and throughout the study that would interfere with the MeDeMSA Care personalized treatment plan or would not permit telemedicine or mobile palliative care;ii.Charlson Comorbidity Index > 4 at the time of consent;iii.Other major underlying medical conditions that may confound interpretation of study results as assessed by the investigator.

We further plan to recruit up to 46 informal caregivers of individuals with MSA participating in the MeDeMSA Care trial, provided they meet the following inclusion criteria:i.Informal caregiver (i.e., a person not receiving payment for caregiving, except for care allowances and tax return schemes available in Austria) of an individual with MSA recruited in the present study;ii.Life-expectancy of at least 24 months, as assessed by the investigator at the time of consent;iii.Aged 18 or older at the time of consent;iv.Understands and agrees to provide information as outlined in the study protocol and to engage in semi-structured online interviews;v.Provides signed and dated written informed consent;vi.Full legal capacity;vii.Fluency in German.

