### Data analysis

The distribution of quantitative data will be assessed using the Shapiro–Wilk test. Quantitative variables will be reported as mean (± SD) for normally distributed data or median (interquartile range, IQR) for non-normally distributed data, and qualitative variables as counts (percentages). Qualitative variables will be compared using Pearson’s Χ^2^ test (or Fisher’s exact test, if n < 5) and quantitative variables using the Mann–Whitney U or t-test, depending on the data distribution. A Benjamini–Hochberg correction will be applied for multiple tests, whenever appropriate. Binary logistic regression with a receiver operating characteristics (ROC) area under the curve (AUC) calculation will follow univariate analysis when applicable.

Changes in EQ-5D, motor, and non-motor scores between the MeDeMSA Care cohort and age-, sex-, and disease duration-matched historical EMSA-SG individuals will be evaluated with ANOVA for repeated measurements or linear mixed models, as most appropriate. Comparisons between randomization groups and the historical cohort will be run on a descriptive basis, with post-hoc tests adjusting for type-1 error based on ANOVA results.

QoL and caregiver burden changes in caregivers of MSA individuals receiving personalized best medical care with or without telemedicine will be analysed with ANOVA or linear mixed models, adjusted for the disease stage of the cared-for individual with MSA. Correlation analyses will assess the relationship between the caregivers’ QoL and burden with the disease characteristics (e.g., symptom constellation and severity) of the cared-for individual with MSA.

Statistical analysis will be performed with SPSS version 30.0.0 or future releases. P values below 0.05 will be considered statistically significant, with 95% confidence intervals considered where appropriate.

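### The primary historical comparison is balanced only on sex, age and disease duration, so the 0.08 EQ-5D target is open to confounding by baseline severity and prognosis, in an unknown direction

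*Protocol article*

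**What the plan says.** All references are to the protocol article.

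- **Endpoint.** Table 1 gives the primary outcome as "Baseline to 18-months EQ-5D-5L score change".
- **Comparator.** Under Study design, the new cohort is "compared to a sex-, age- and disease-duration matched historical European MSA cohort that received standard care". Table 1 and Analysis sets and subgroups set the tolerances at 5 years for age and 12 months for duration.
- **Fallback.** If suitable controls are lacking, Analysis sets and subgroups allows "an alternative matching approach by categorizing individuals into subgroups based on age" (below 60 against 60 or more) and disease duration (below 3 years against 3 or more). Footnote a of Table 1 says the same. Neither place restates sex.
- **Model.** Under Data analysis, changes between the cohorts "will be evaluated with ANOVA for repeated measurements or linear mixed models, as most appropriate". No covariate is named. The caregiver analysis in the same section is adjusted for the patient's disease stage.
- **Entry to the new cohort (Population).** Inclusion requires "Life-expectancy of at least 24 months as assessed by the investigator at the time of consent" and "Diagnosed with clinically probable OR clinically established MSA according to the current criteria", the latter cited to a 2022 source. A candidate is excluded for "Charlson Comorbidity Index > 4 at the time of consent" or for another major condition that could confound the results. The historical cohort is cited to 2013. The article does not say whether its records will be screened against these criteria.
- **Stage and phenotype.** Stage stratifies the telemedicine randomisation. Stage and phenotype define subgroups of the new cohort. Neither enters the historical contrast.

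**The concern.** Randomisation here answers only the telemedicine question. For the primary question, matching is the only safeguard of comparability that the article states. Two patients of the same sex, age and disease duration may differ in whether they walk or use a wheelchair, in phenotype, and in starting EQ-5D. Any of these may go with a different expected decline over 18 months.

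Selection may differ as well. The new cohort is chosen partly on expected survival beyond the 18-month endpoint and on limited comorbidity; the article does not put the historical pool through the same filter. New patients who cannot walk or stand unaided must also live where mobile palliative care exists in Austria, so the stage mix is shaped locally, whereas the historical cohort came from ten countries. The statement under Study design that characteristics were largely comparable concerns those countries among themselves, not the historical cohort against the new one.

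At stake is whether a difference near 0.08 could be credited to the care programme, or its absence held against it.

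**Working it through.** **1. The plan's own target.** From Sample size calculation: historical mean 0.35 at baseline and 0.17 at 18 months; hoped-for value 0.25 at 18 months.

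- Historical decline: 0.35 − 0.17 = 0.18.
- Decline under the programme if it also starts at 0.35: 0.35 − 0.25 = 0.10.
- Difference in change: 0.18 − 0.10 = 0.08, which reproduces the stated target.

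The difference in 18-month levels (0.25 − 0.17) equals the difference in change only if both groups start at the same EQ-5D. The matching does not secure this. The 95% interval for the historical baseline mean is 0.27 to 0.42, a half-width of (0.42 − 0.27)/2 = 0.075, nearly the whole target.

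**2. What matching leaves open.** Under the fallback, a 61-year-old and an 80-year-old fall in the same age band. Within the main tolerances, nothing separates ambulant from wheelchair-bound patients.

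**3. Illustrative effect of a residual imbalance.** Inputs: 46 enrolled with 10% dropout gives 46 × 0.9 ≈ 41; SD 0.25; two-sided 5% test; no true effect. One control per case is my assumption, as the article gives no ratio. With b the leftover difference in expected change:

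SE = 0.25 × √(2/41) = 0.055; P(false result favouring the programme) = 1 − Φ(1.96 − b/SE).

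The last column treats the historical mean as fixed, so SE = 0.25/√41 = 0.039.

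| b (assumed) | 1:1 controls | fixed historical mean |
|---|---|---|
| 0 | 2.5% | 2.5% |
| 0.02 | 5.5% | 7.4% |
| 0.04 | 10.8% | 17.5% |
| 0.06 | 19.1% | 33.6% |
| 0.08 | 30.5% | 53.5% |

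The values of b are assumptions; the article supplies none. A negative b would hide a real effect instead.

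**4. Direction.** Three plausible mechanisms do not agree.

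- *Prognosis and comorbidity filter on one side only:* favours the programme. If a share p of controls would fail the criteria and decline d more, the bias is p × d. Assumed values give 0.10 × 0.15 = 0.015 up to 0.30 × 0.30 = 0.09. The top end is extreme: with an overall mean decline of 0.18, the other 70% would decline 0.18 − 0.09 = 0.09 and the failing 30% would decline 0.39, more than the mean baseline score.
- *Higher starting EQ-5D in the new cohort:* works against the programme under regression to the mean. With baseline gap g and follow-up-on-baseline slope β, the change-score bias is g × (β − 1). Assumed values give 0.05 × (0.7 − 1) = −0.015 to 0.10 × (0.5 − 1) = −0.05. This requires one common regression line for both cohorts.
- *Retention:* Potential study limitations notes that severe cases may be kept who would probably have been lost in the historical study. This also works against the programme.

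**The case against.** Several counter-arguments have force.

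- **The contrast is not shown to be confounded.** A reader might infer that it is confounded by severity and that the bias flatters the programme. The article has no data on imbalance, and step 4 shows forces in both directions. This stands: open to confounding is as far as the text goes.
- **A change score already removes the starting level.** Correct. What remains is decline that depends on baseline status or prognosis. Duration matching may also capture some severity, since the Introduction links time from onset to disability. That reduces the problem without removing it.
- **Baseline adjustment is itself an assumption.** If the cohorts come from populations with different means, each regresses to its own mean, and adjusting can introduce bias (Lord's paradox). This stands, and is the reason to report both analyses.
- **Covariates may be in an analysis plan that is not shown.** Silence on covariates alone would be no finding. But the matching set and its fallback are fixed in the article, and the same section does name an adjustment where one is intended, for caregivers.
- **The historical entry criteria are unknown.** A reader might infer that the historical cohort had no prognosis or comorbidity limits. The article does not say. It shows only that the present criteria are not stated to be applied to it; criteria cited as 2022 cannot have governed entry to a cohort published in 2013.
- **Sex in the fallback.** A reader might infer that sex matching is abandoned. The text relaxes age and duration and does not mention sex; the intention is unclear.

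**Conclusion.** The point holds in a limited form. The only stated protection for a non-randomised primary comparison is matching on three variables, with a coarse fallback. Severity, stage, phenotype and baseline EQ-5D are left out of both matching and stated model, and the new entry criteria are not stated to be carried over to the controls. The 0.08 target is therefore open to confounding by baseline severity and prognosis. Size and direction are unknown; the figures in steps 3 and 4 are illustrations under assumed inputs, not estimates. The conclusion itself does not depend on them: it rests on the stated matching set and on there being no randomised control for the primary question.

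**What to change.** 1. **Primary model.** Analyse 18-month EQ-5D (or use a mixed model) on cohort, with baseline EQ-5D, phenotype, sex, continuous age, continuous disease duration, and either one baseline motor-severity measure or early/advanced stage. Do not enter several overlapping severity terms with only about 41 expected completers in the new cohort. Report the unadjusted matched change-score contrast as a sensitivity analysis, so that dependence on the adjustment is visible.
2. **Fallback.** Replace the 60-year and 3-year bands by all eligible historical controls with this adjustment, or by propensity weighting, keeping sex and continuous age and duration.
3. **Historical pool.** Before matching, apply those entry criteria that can be derived from stored baseline data. Do not select on observed survival. State which criteria could not be applied: investigator-judged life expectancy is unlikely to be recoverable, and nothing shows that the Charlson index or the 2022 diagnostic category can be derived.

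**Cost.** Analysis-plan wording and a review of records already held at the sponsor's institution. EQ-5D and motor scales are due to be compared with that cohort anyway, so these covariates should be available. Some controls may be lost, and the adjusted estimate carries a modelling assumption. No patient procedure changes. With 23 of 46 patients recruited by March 2025, these choices are best fixed before outcomes are compared, so that they do not look data-driven.
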